### Selection and Exclusion of Participants From Study

The inclusion criteria will be patients aged 75 years and older, male or female, living in their own home or a care facility (including independent-living facilities), hospitalized in short-stay geriatric care, and with confirmed receipt of information on the study and their rights, as stipulated by articles L.1122-1 of the French public health code, by 57 of the “Informatique et Libertés” data protection act, and by MR-003 of the French data protection and civil liberties authority (CNIL). The exclusion criteria will be patients aged younger than 75 years or refusing to participate.

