### Recorded Variables and Source Data

The study data will be collected directly from the questionnaires as the study progresses. For the first questionnaire (context of calls and solutions proposed), filled out by the hotline geriatric specialist (Textbox 1), health and administrative information will be collected for the study. The health data collected will include the identification of both speakers on the call, patient age, reasons for calling, degree of emergency as perceived by the geriatric specialist and the calling doctor (evaluated by simple scale from 0 to 10; 0 being a null degree of urgency and 10 an absolute urgency), and the responses offered by the geriatric specialist. The administrative data will include call duration (in minutes).

This questionnaire will be anonymous with no identifying criteria. It will be filled out every time contact is made via the hotline, irrespective of what responses are offered by the doctor (referrals to short-stay geriatric care or not).

For the second questionnaire, filled out by the geriatric specialist treating the patient during their hospitalization in short-stay geriatric care following referral from the hotline (Textbox 2), the sociodemographic, health, family, living situation, and location information will be collected for the study.

Sociodemographic data will include the first and last name of the patient, Patient Permanent Identification number, and patient age. These data will be anonymized on entry.

The health data collected will be the reason for hospitalization; number of hospitalizations during the past year; polypharmacy (four or more medications at the same time); biological data [17], including albumin and C-reactive protein levels for assessing nutritional status; and Charlson Comorbidity Index calculation using patient history for assessing the comorbidities of our geriatric population [18-20]; evaluation of activities of daily living (ADL) before hospitalization according to the validated ADL (/6) [21] and instrumental ADL scales (/4) [22]; evaluation of cognitive status using the Mini-Mental State Examination score (/30) [23]; and recommended referral after hospital discharge.

We chose the Charlson Comorbidity Index because it is a validated, reproducible, and simple comorbidity score that measures the impact of age (as there is excess mortality according to age), weighting by age from 1 (50-59 years) to 5 (90-99 years). This score is widely used for geriatrics publications.

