**Charlson Comorbidity Index score, mean (SD)**

**Previous autonomy**
Mean activities of daily living (SD)Mean instrumental activities of daily living (SD)Mean blood albumin (SD)Mean C-reactive protein (SD)

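### The only comorbidity index is an age-weighted Charlson total, so unadjusted comparisons of comorbidity partly reflect age; the effect is modest and the correction is free

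*Protocol article*

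**What the plan says.** All of this is in the protocol article.

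- **Purpose.** Methods, Recorded Variables and Source Data, lists a "Charlson Comorbidity Index calculation using patient history for assessing the comorbidities of our geriatric population".
- **Reason for the choice.** The same section explains that the index "measures the impact of age (as there is excess mortality according to age), weighting by age from 1 (50-59 years) to 5 (90-99 years"; it adds that geriatric publications use it widely.
- **Reporting.** The list for the second questionnaire (sociodemographic participant characteristics) has one line for it: "Charlson Comorbidity Index score, mean (SD"). No line shows the score without its age points.
- **Age.** It is collected in its own right: "Sociodemographic data will include the first and last name of the patient, Patient Permanent Identification number, and patient age". Mean age is also its own reporting line.
- **Population.** "The inclusion criteria will be patients aged 75 years and older, male or female", with no upper age limit.
- **Related variables.** The second questionnaire also records "polypharmacy (four or more medications at the same time") and diagnosed dementia, plus albumin, C-reactive protein, ADL, instrumental ADL and the Mini-Mental State Examination.
- **Analysis.** Statistical Analysis plans comparisons of hotline patients by sex and type of discharge at the 5% level, analyses within each center, generalized linear and mixed models, and a patient-profile analysis. It names no covariates for the models and no inputs for the profile analysis.

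**The concern.** The stated purpose is to assess comorbidity. The stated reason for choosing this version is that it captures age and age-related mortality. Age points suit a prognostic score, but they get in the way when the score is meant to describe disease burden and age is already available as a separate variable.

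The univariate comparisons by sex and type of discharge are unadjusted. If women are older than men, or patients discharged to a nursing home are older than those going home, the total score will differ between them even when their diseases are the same. A reader of the results table would take that as a comorbidity difference. The same applies when centers with different age mixes are set side by side.

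What is at stake is how one descriptive variable is read. It contributes to the secondary endpoint on health status and to the patient profile. The primary endpoint, mean duration of stay, is not affected.

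**Working it through.** **1. Age points under the stated weights.** Input: 1 point at 50-59 rising to 5 at 90-99 (Recorded Variables and Source Data). One point per decade, floor(age/10) − 4, gives 1, 2, 3, 4, 5 for the decades starting at 50, 60, 70, 80 and 90, which matches both stated ends. In this population:

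- 75-79 years: 3 points
- 80-89 years: 4 points
- 90-99 years: 5 points

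The lowest value, 3, is shared by everyone and drops out of any difference. The largest difference due to age alone is 5 − 3 = 2 points. The stated scale gives no weight at 100 and over.

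**2. Share of the score due to age.** The article gives no age or Charlson distribution, so these inputs are assumed: normal ages truncated to 75-99, disease points independent of age, and a disease-point SD of 1.5 to 3. Across three assumed age distributions the variance of the age points was 0.295 to 0.369.

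- Largest share: 0.369 / (0.369 + 1.5²) = 0.14
- Smallest share: 0.295 / (0.295 + 3²) = 0.03

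So about 3% to 14% of the variance of the total is age. The total correlates 0.93 to 0.98 with its disease part and about 0.15 to 0.33 with age.

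**3. Difference between two groups with equal disease burden.** Assumed: age SD 6 before truncation. Mean age points = 4 + P(90-99) − P(75-79).

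| Mean age | P(75-79) | P(90-99) | Mean age points |
|---|---|---|---|
| 84.8 | 0.198 | 0.169 | 3.97 |
| 85.5 | 0.164 | 0.206 | 4.04 |
| 86.1 | 0.139 | 0.241 | 4.10 |
| 87.1 | 0.103 | 0.305 | 4.20 |

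Against the group with mean age 87.1, the differences are:

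- 1.0-year gap: 4.20 − 4.10 = 0.10 points
- 1.6-year gap: 4.20 − 4.04 = 0.16 points
- 2.3-year gap: 4.20 − 3.97 = 0.23 points (0.24 in a separate simulation)

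**4. In SD units.** Total SD = √(disease SD² + 0.6²), with 0.6 for the age points (√0.369 ≈ 0.6). For disease SDs of 1.5 and 2.5 this is 1.62 and 2.57.

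- 0.10 points: 0.10/2.57 = 0.04 to 0.10/1.62 = 0.06 SD
- 0.16 points: 0.16/2.57 = 0.06 to 0.16/1.62 = 0.10 SD
- 0.23 to 0.24 points: 0.23/2.57 = 0.09 to 0.24/1.62 = 0.15 SD

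**5. Chance of a significant result at this sample size.** The article gives about 250 per center in seven centers (7 × 250 = 1750) and 2000 in total, so both totals are used, with an assumed 60:40 split and a two-sided 5% z-test. Example: 2000 patients, disease SD 1.5, 0.16 points. The standard error is 1.62 × √(1/1200 + 1/800) = 0.074, z = 0.16/0.074 = 2.2, and the chance of P<.05 is about 58%. With 1750 patients and disease SD 2.5, the standard error is 2.57 × √(1/1050 + 1/700) = 0.125, z = 1.28, and the chance is about 25%. The ranges are:

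- 1.0-year gap: about 13% to 27%
- 1.6-year gap: about 25% to 58%
- 2.3-year gap: about 45% to 88%

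A difference due wholly to age could thus often be flagged as significant, because the sample is large, not because the difference is.

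**The case against.** The case for leaving the plan alone is substantial, and most of it stands.

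- **The choice is disclosed and deliberate.** The article says that the score includes age and why. This is neither an error nor a contradiction. The point made here is only that the choice fits the stated purpose poorly.
- **The analysis plan may deal with it.** That plan is not shown, and its absence is no finding. But the article does more than stay silent: it picks the age-weighted version and lists only the total. That stated choice is open to comment.
- **The effect is small.** A difference of 0.04 to 0.15 SD is minor, and the total tracks the disease part closely. The rejection rates in the working are measured against a null of equal disease burden. As a test of the score actually chosen, the test correctly detects a real difference.
- **Comorbidity is not measured by Charlson alone.** Polypharmacy and diagnosed dementia are also recorded. Neither measures overall disease burden, so Charlson remains the only comorbidity index.

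A reader might go further in two ways that the article does not support.

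1. *That age is counted twice in the models.* No covariates or profile inputs are named, so this cannot be asserted. Even if both entered a linear model, age would absorb most of the age points. With the assumed variance of 0.369 and a correlation of 0.88 between age and age points, the variance left over is 0.369 × (1 − 0.88²) = 0.083. The Charlson coefficient would shrink only by the factor 2.25/2.333 = 0.96 (disease SD 1.5) to 6.25/6.333 = 0.99 (disease SD 2.5).
2. *That the answer on whether hotline patients are less fragile is biased.* The Discussion states that the study has no comparison, so there is no group admitted through the emergency department for age points to distort. That question also rests on autonomy, which ADL and instrumental ADL cover.

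**Conclusion.** The point holds as a minor one. The only comorbidity index mixes disease burden with age, only the total is listed, and the planned comparisons by sex and type of discharge are unadjusted. Where those groups, or the centers, differ in age, part of any Charlson difference is age. Two patients aged 75-99 can differ by at most 2 points for this reason. For assumed mean-age gaps of 1 to 2.3 years the group difference is about 0.10 to 0.24 points, or 0.04 to 0.15 SD.

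The 3, 4 and 5 age points follow from the article's own weights. The group differences rest on assumed age distributions, disease-point SDs and age gaps, and on disease points being independent of age. The article does not say whether the compared groups differ in age; if they do not, the effect vanishes. The missing weight at 100 and over is a marginal scoring detail, not a separate problem.

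**What to change.** Add one sentence to Statistical Analysis and one derived variable:

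- Derive the Charlson score without age points by subtracting, from each total, the age points implied by recorded age (3 at 75-79, 4 at 80-89, 5 at 90-99). For anyone aged 100 or over, subtract whatever age weight was used in scoring, or sum the disease points directly. The derived score then needs no age weight at any age.
- Use this score as the comorbidity variable in the comparisons by sex, type of discharge and center, and in the patient-profile analysis, with age as its own variable.
- Keep the age-weighted total as a descriptive line, so that comparability with other geriatric publications is retained.

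The cost is close to nil. No new data, visits or patients are needed, and the primary endpoint and sample size do not change.

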**Caller**
General practitionerHospital physicianOther
**Hotline responding doctor**
Assistant physicianHospital practitioner
**Reason for calling**
AdviceEmergency department hospitalizationEmergency geriatric department hospitalizationConsultation requestDeferred hospitalization
**Patient age (years), mean (SD)**

**Degree of emergency perceived by the hotline doctor, mean (SD)**

**Degree of emergency perceived by the calling doctor, mean (SD)**

**Response**
Simple adviceMedicalSocial-medicalTherapeuticEmergency admissionTo emergency department:No beds in short-stay geriatricsEmergency care requiredShort-stay geriatric care: allocated bedYesNoDeferred hospitalization (days), mean (SD)Nonhospital ambulance servicesOutpatient careConsultationTeleconsultationTemporary nursing home
**Call duration (minutes), mean (SD)**

Sociodemographic participant characteristics.
**Mean age (SD)**

**Sex**
MaleFemale
**Mean hospitalization duration (SD)**

**Type of living area**
UrbanSemiurbanRural
**Reason for hospitalization**
FallFaintingFrailtyDifficulties coping at homePainStrokeChange in general statusConfusion or behavioral problemsBreathing difficultiesSepsisOther (specify)
**Residence type**
Own homeNursing homeIndependent-living facility
**Family or marital situation**
With a partnerAlone no childrenAlone with childrenOther
**Polypharmacy (>4)**
YesNo
**Charlson Comorbidity Index score, mean (SD)**

**Previous autonomy**
Mean activities of daily living (SD)Mean instrumental activities of daily living (SD)Mean blood albumin (SD)Mean C-reactive protein (SD)
**Cognitive disorder**
Mean Mini-Mental State Examination score (SD)Diagnosed dementia
**Walking difficulties**
Walking aidsHistory of falls
**Outcomes**
Return homeReturn to nursing homeLong-term rehabilitationFollow-up care then nursing homeAdmission to nursing homeAdmission to independent-living facilityDeathReturn home with planned help (specify)

### Statistical Analysis

This is a pilot study. Given the need for subgroup analyses and information concerning the activities conducted at the investigating centers participating in this study, approximately 250 patients are required per center (ie, 2000 in total). This goal is attainable in 24 months, which represents the entire duration of the study. Statistical analysis will be done by statisticians. Different measures will be used depending on the desired descriptive statistics. All analyses will be conducted on the entire included population and each investigating center.

Univariate analysis, descriptive analyses of the study population, will involve recorded variables, comparison of subjects included via the hotline according to sex, and type of discharge using parametric or nonparametric tests and according to the distribution of variables (chi-square tests for quantitative variables, Student *t* tests for qualitative variables, test significance set at 5%).

Multivariate analyses will include analyses of mean values (ANOVA), the use of a generalized linear model, the use of a mixed model for taking into account the random effect of choosing seven centers. A multiple-component analysis will be used to identify different patient groups (patient profile analysis).

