**Methods:**

The study will be conducted over 24 months in seven French university hospital centers. It will include all patients aged 75 and older, living in their own homes or nursing homes, who are admitted to short-stay geriatric wards following hotline consultation. Two questionnaires will be filled out by medical staff at specific time points: (1) after conducting the telephone consultation and (2) on admitting the patient to a short-stay geriatric medical care. The primary endpoint will be mean hospitalization duration. The secondary endpoints will be intrahospital mortality rate, the characteristics of patients admitted via the hotline, and the types of questions asked and responses given via the hotline.

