## Methods

### Design and Setting

This will be a multicenter descriptive study conducted in seven French investigating centers (including university centers, across three different regions) with subgroup analysis (Table 1). Participating establishments will all be voluntary. To participate in the study, the center must have a specific and separate telephone line for doctor-doctor communications. Only calls originating from health care professionals will be included. The study will last for 24 months (May 2018 to May 2020). The course of the study and its design are presented in Figure 1.

Two questionnaires will be distributed at two distinct time points: after telephone consultation (hotline) and after admission to a short-stay geriatric ward. The first questionnaire will be filled out via the hotline by the geriatric specialist answering the call. A second questionnaire will then be filled out during the patient’s hospitalization by the treating geriatric specialist.

**Table 1 table1:** Description of geriatric care offered by different participating centers.

Paticipating center	Residents, n	Hospital beds, n	Short-stay geriatric care	Postdischarge care	Long-term rehabilitation care	Consultation	Outpatient clinic	Ambulance care	Telemedical consultation
Bordeaux	252,000	3076	x	x	x	x	x	x	x
Clermont-Ferrand	141,400	2136	x	x	x	x	x		
Saint Etienne	171,100	1819	x	x	x	x	x	x	x
Angers	151,500	1445	x	x	—^a^	x	x	x	x
Lyon Sud	513,300	1038	x	x	x	x	x	x	—
Saint Chamond	34,870	710	x	x	—	x	—	x	—
Firminy	16,840	475	x	x	x	x	x	x	—

^a^Service not offered.

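### The stated sample size contradicts itself: about 250 patients in each of seven centres is 1750, not 2000

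*Protocol article*

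**What the plan says.** The sample size is stated once, in the Statistical Analysis section: "approximately 250 patients are required per center (ie, 2000 in total". The reason given is "Given the need for subgroup analyses and information concerning the activities conducted at the investigating centers participating in this study", which is an argument about how many patients each centre should contribute. The next sentence adds: "This goal is attainable in 24 months, which represents the entire duration of the study".

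The number of centres is consistent throughout:
- Abstract, Methods: "The study will be conducted over 24 months in seven French university hospital centers".
- Design and Setting: "This will be a multicenter descriptive study conducted in seven French investigating centers".
- Table 1: seven named centres.
- Statistical Analysis, the same section as the sample size: "the use of a mixed model for taking into account the random effect of choosing seven centers".

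**The concern.** The total is offered as a restatement of the per-centre requirement, but the two figures agree only if there are eight centres, and the article describes seven. A reader cannot tell which number governs: the per-centre figure, which carries the rationale, or the overall total.

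This matters for three reasons. The sentence is the article's only statement of sample size. Analyses are planned both on the whole population and within each centre, so the per-centre and overall figures each have a use. And the claim that the goal can be reached in 24 months has no definite meaning while the goal itself has two values. When the results are reported, recruitment of 1750 patients could be described either as meeting the plan or as missing it.

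**Working it through.** **Inputs, all from the protocol article**
- Patients per centre: approximately 250 (Statistical Analysis).
- Total: 2000 (same sentence).
- Centres: 7 (abstract; Design and Setting; Table 1; Statistical Analysis).
- Recruitment period: 24 months (abstract; Design and Setting; Statistical Analysis).

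**Step 1. Try to reproduce the stated total.** Total = centres × patients per centre = 7 × 250 = 1750. The stated 2000 is not reproduced. The difference is 2000 − 1750 = 250 patients, and 250/2000 = 12.5%.

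**Step 2. Find what would give 2000.**
- Keep 250 per centre: 2000/250 = 8 centres.
- Keep seven centres: 2000/7 = 285.7, so about 286 per centre. That is 285.7/250 − 1 = 14.3% above the stated requirement, or about 36 more patients per centre.

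**Step 3. Test the charitable readings.**
- *Rounding.* With seven centres, a total within 3% of 2000 (1940 to 2060) needs 278 to 294 per centre. An author with such a figure in mind would not normally write approximately 250.
- *Dropout.* Inflating 1750 by 1/(1 − d) gives 1843 at d = 5%, 1945 at 10%, 2000 at 12.5% and 2059 at 15%. Only 12.5% gives 2000 exactly. No dropout rate is stated, and the Study Endpoint section ends participation at discharge from the ward.
- *Unequal quotas.* None is stated; the figure is given per centre.
- *An eighth centre.* None appears anywhere.

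**Step 4. Monthly recruitment implied by each resolution.**
- 250 per centre: 250/24 = 10.4 patients per centre per month.
- 2000 over seven centres: 285.7/24 = 11.9 patients per centre per month.

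**Step 5. Effect on precision.** A confidence interval for a mean narrows with the square root of n. At 1750 it is √(2000/1750) = 1.069 times as wide as at 2000, about 7% wider whatever the SD. The article gives no SD for length of stay. Assuming 9 days (range 7 to 11) and ignoring clustering, the 95% half-width 1.96 × SD/√n is:

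| n | SD 7 | SD 9 | SD 11 |
|---|---|---|---|
| 1750 pooled | 0.33 | 0.42 | 0.52 |
| 2000 pooled | 0.31 | 0.39 | 0.48 |
| 250 in one centre | 0.87 | 1.12 | 1.36 |
| 286 in one centre | 0.81 | 1.04 | 1.27 |

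All half-widths are in days. At SD 9 the difference is about 0.03 days pooled and 0.08 days within a centre.

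**The case against.** The strongest reply accepts the arithmetic and disputes its consequence. A reader might infer that centres recruiting to 250 would leave the study 12.5% short of its target. The article does not support that. The abstract says that every eligible patient admitted after a hotline consultation will be included, over a fixed 24 months. Enrolment is therefore set by the calendar and by the flow of eligible admissions, and nothing tells a centre to stop at 250. Both figures read as expected or minimum numbers. This objection stands: no recruitment shortfall is demonstrated.

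The second reply is that nothing inferential depends on the total. The study is called a pilot and descriptive, its limitations state that there is no comparison, and no effect size, SD, power or precision target is attached to either figure. This also stands, and the precision differences above are too small to alter a conclusion about mean length of stay.

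Two further inferences should be resisted. Because 2000 is exactly 8 × 250, one might suppose that the total survives from a plan with eight centres. That is possible, but the article does not say so. One might also suppose that the higher monthly rate is not feasible. The article gives no past admission or recruitment rate, so it cannot show that 10.4 per month is attainable and 11.9 is not.

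The word approximately helps the article least. It loosens the 250, but it does not cover a 14% gap between figures presented as equivalent.

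**Conclusion.** The point holds as an internal contradiction in the only stated sample size. With seven centres, 250 per centre gives 1750, and 2000 gives about 286 per centre. The discrepancy is 250 patients, or 12.5% of the stated total. The finding rests only on the article's own figures; the SD used to illustrate precision is an assumption, and the finding does not depend on it.

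The article does not show which of the three numbers is wrong. The per-centre figure has the better claim to govern, because the stated rationale concerns subgroups and individual centres, but that is a judgement and not proof.

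The weight is moderate: a stated sample size needs correcting, but the expected effect on the conclusions is small.

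**What to change.** Reconcile the per-centre figure, the total and the number of centres in the Statistical Analysis section:

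- If the per-centre requirement governs, state approximately 250 patients per centre in seven centres, 1750 in total. This changes one number and needs no additional patients beyond the stated per-centre requirement.
- If 2000 is the real target, state about 286 patients per centre in seven centres. This raises the stated requirement by about 36 patients per centre, or 14%.

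Then make the 24-month attainability statement refer to the figure chosen: about 10.4 patients per centre per month for 1750, or about 11.9 for 2000. Either way the cost is an edit of one or two sentences. The design, the data collection and the analysis methods stay as they are.

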### Evaluation Criteria

The primary endpoint is the mean duration of hospitalization in short-stay geriatric care. The secondary endpoints are hospital mortality rate, assessment of health status of elderly patients hospitalized in short-stay geriatric wards using different criteria and their outcomes following discharge, describing and comparing how the different hotlines across France function, analyzing the principal responses provided to doctors using the hotline, and improving awareness.

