By analyzing center by center, we will be able to describe each center with the different responses they offer. Ideally, this will help to improve the function of the geriatric hotline for the entire country and pave the way to new advances, especially in the organization of the care path in the long run.

The analysis also will be conducted in two sections. First, the call to the hotline will be analyzed. Did the experience of the doctor responding to the call influence the type of care recommended and the response offered? Does a high level of perceived emergency correlate to hospitalization via the ED? Is the hotline solely used by general medicine doctors? Would it be a good idea to roll out access to the hotline to other hospital specialties? Given the growing issue of population aging, the current geriatric services are not enough to care for all the elderly. This is why specialists are turning more toward other fields for geriatric assessment (eg, oncology, orthopedics). This study will reveal the different responses that can be provided by this tool (the hotline), from therapeutic or medical advice to referrals for hospitalization, ambulance call-outs, consultations, telemedicine, and more.

Second, we will study the profile of patients referred for hospitalization via the hotline to determine the characteristics of those the hotline recommends for admission to improve their health care approach. Does this tool lead to direct hospitalization in short-stay geriatric care for the less-fragile patients who still have some autonomy? Are the motives for admission less serious? We hypothesize that the mean duration of hospitalization will be shorter in cases in which it is planned, which leads to the question of whether the future of hospitalization is influenced by the ways patients are admitted. In their study involving 520 patients, Dijon et al [27] demonstrated that the intrahospital care pathways of geriatric patients referred directly to short-stay geriatric care are shorter and more effective than those experienced by patients who first went through EDs, with significantly shorter mean hospitalizations achieved through direct hotline-referred admissions (11.6 days versus 14.1 days with ED consultation; *P*<.05). Patients admitted to short-stay care via EDs were also the quickest to be rehospitalized in the future.

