Another advantage of our study is its innovative character because there are currently very few studies analyzing geriatric hotlines [25]. In addition, it is observational in nature, which enables many types of procedures from across the country to be analyzed, leading to more standardized approaches.

The study does have limitations, notably its nonrandomized nature. There is no comparison because it is a descriptive study. The quality of the responses will be operator-dependent. Eventually, the goal will be to conduct a second study aiming to compare profiles of elderly patients hospitalized in short-stay geriatric wards via EDs versus those referred via a geriatric hotline. Through the first questionnaire, we will analyze the different responses provided by the hotline (eg, call-outs, consultations, telemedicine, day hospital). We will evaluate the number of hospitalizations avoided or deferred in time following the use of the hotline to reduce inappropriate passage through EDs.

This first study will demonstrate if managing patients by means of a geriatric hotline offers the most effective approach and results in shorter mean hospitalization durations and thus fewer complications and geriatric syndromes and fewer trips to EDs. It will also describe and compare the function of different geriatric hotlines across France to improve health care pathways for the elderly and pave the way toward future advances, such as new modalities of patient management, the development of more appropriate responses to this population, and the reduction of inappropriate visits to emergencies, which we know can be deleterious for the elderly.

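### The promised conclusion that hotline referral is the most effective management, shown by shorter stays, cannot follow from a one-group mean and 5% tests by sex and discharge type

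*Protocol article*

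**What the plan says.** Evaluation Criteria: "The primary endpoint is the mean duration of hospitalization in short-stay geriatric care". No reference value, comparator or test is attached, and under Participants everyone studied has been referred by the hotline.

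Statistical Analysis: "Univariate analysis, descriptive analyses of the study population, will involve recorded variables", followed by a "comparison of subjects included via the hotline according to sex, and type of discharge using parametric or nonparametric tests", with "test significance set at 5" per cent. ANOVA, a generalized linear model and a mixed model with a random centre effect are then listed, without an outcome or contrast for any of them.

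Hypotheses: the Introduction expects shorter stays because unnecessary ED time is avoided. The Discussion adds: "We hypothesize that the mean duration of hospitalization will be shorter in cases in which it is planned".

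Conclusions promised: the Abstract's Conclusions and the opening and closing paragraphs of the Discussion say that the study will establish whether the hotline is effective, or the most effective, management. The Abstract and the closing paragraph tie this to shorter mean stays. The limitations paragraph of the same Discussion says: "There is no comparison because it is a descriptive study". It defers a comparison of hotline and ED admissions to a second study.

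**The concern.** Shorter is a comparative word, and the design supplies nothing to be shorter than. The comparisons that are planned, by sex and by discharge type, do not bear on how the patient reached the ward. The final report would therefore have a primary result that cannot answer the question posed in the Abstract, beside a set of 5% tests that answer other questions. The risk is that a mean stay is presented as evidence of effectiveness, or that an incidental difference significant at 5% is presented as the study's finding.

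**Working it through.** **Step 1. Set the conclusion against the analysis.**

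| Element | What the protocol article gives | Can it show a shorter stay due to the hotline? |
|---|---|---|
| Primary endpoint | One mean, hotline patients only | No: no comparator or reference value |
| Tests by sex | Men versus women, all hotline patients | No: not a route of admission |
| Tests by discharge type | Groups known only when the stay ends | No: not a route of admission |
| ANOVA, generalized linear model, mixed model | No outcome or contrast named | Not as stated; centre is a random effect among hotline patients |

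Could the hypotheses be tested inside the hotline cohort? Deferred hospitalization and referral to the ED are recorded on the first questionnaire (first textbox). Recorded Variables and Source Data describes that form as anonymous, without identifying items, so as described it cannot be linked to an individual's ward stay. The second questionnaire lists no item for planned admission or ED passage.

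The Discussion cites an earlier study of 520 patients with mean stays of 11.6 days (direct) and 14.1 days (via the ED). The article does not designate either figure as a reference value.

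**Step 2. Count the tests at 5%.** The article states no family-wise rate, so there is no figure of its own to reproduce.

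The second textbox lists 18 patient-level variables: age, sex, length of stay, living area, reason for hospitalization, residence, family situation, polypharmacy, Charlson index, ADL, instrumental ADL, albumin, C-reactive protein, Mini-Mental State score, dementia, walking aids, falls and outcome. Recorded Variables and Source Data adds hospitalizations in the past year, which makes 19.

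- By sex: 19 − 1 = 18 tests.
- By discharge type: 19 − 1 = 18 tests.
- Sex by discharge type is counted twice: 18 + 18 − 1 = 35 distinct pooled tests.

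**Step 3. Error rates, pooled sample, all nulls true.**

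Expected false positives: 35 × 0.05 = 1.75.

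Family-wise rate if independent: 1 − 0.95^k. For k = 35, 1 − 0.95^35 = 0.834. For correlated tests I used two-sided normal statistics with one common correlation ρ, by numerical integration.

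| True nulls tested | ρ = 0 | ρ = 0.5 | ρ = 0.8 |
|---|---|---|---|
| 35 (all) | 83% | 54% | 27% |
| 25 | 72% | 47% | 24% |
| 18 (sex only) | 60% | 40% | 22% |

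Under independence the rate passes one half between 13 tests (48.7%) and 14 tests (51.2%).

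**The case against.** The strongest reply is that the study is labelled pilot and descriptive, that the tests are introduced as descriptive analyses of the population, and that a single-group mean needs no contrast to be estimated. Test hierarchy and multiplicity rules also commonly sit in an analysis plan, which is not shown. All of this stands. A missing multiplicity rule is therefore not the point, and strict error control in such a study is a trade-off, not a requirement. The reply does not remove the mismatch between the published conclusions and the design: an analysis plan could not supply a comparison group that the article says does not exist.

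It can also be said that the article promises only to find out *if* the hotline is more effective, not that it is. That is fair, but a one-group mean cannot answer the question in either direction.

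Two stronger readings are tempting and not supported:

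- A reader might infer that a chance significant result is more likely than not. That requires every recorded variable to be tested (the text says only that recorded variables are involved), all nulls true, and at most moderate correlation. The rate is 27% at correlation 0.8. Some discharge-type nulls are probably false: the outcome categories separate return home from return to a nursing home, so residence is associated with outcome almost by construction.
- A reader might infer that sex, discharge type, centre, planned status and area type compete as contrasts for the primary endpoint. Only sex and discharge type are named as group comparisons. Planned status sits on the anonymous form, area type is discussed in relation to knowledge of and access to the hotline, and centre enters as a random effect and for description.

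**Conclusion.** The point holds as a contradiction within the document. The endpoint has no comparator, the named tests address neither hypothesis, and the limitations paragraph disclaims comparison, yet the Abstract and Discussion promise a comparative conclusion about stay. This part rests on the text alone and needs no statistical assumption.

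The multiplicity figures are secondary and conditional. With up to about 35 pooled tests and all nulls true, about 1.75 false positives are an upper figure for the expected number. The family-wise rate ranges from 27% to 83% over correlations from 0.8 to 0, and falls as true associations replace nulls. This is enough to say that these tests should not stand in as the study's result. It is not evidence of an error in a confirmatory test, because none is specified. The change is worth making before analysis.

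**What to change.** 1. In Statistical Analysis, state that the primary analysis is estimation: mean ward stay among hotline patients with a 95% CI from the mixed model already planned (random centre), and no hypothesis test on the primary endpoint.
2. Label the comparisons by sex and by discharge type exploratory and report them as differences with 95% CIs. False discovery control across the family is optional.
3. Show length of stay by discharge type descriptively only, since discharge type is known only when the stay ends.
4. Reword the Abstract's Conclusions and the opening and closing paragraphs of the Discussion so that they claim a description of stay among hotline patients. Leave comparative effectiveness to the second study that the Discussion announces.

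The cost is a few sentences and minor changes to the analysis code, with no new data or patients. The downside is that fewer differences will be called significant and the conclusion will be more modest.
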